## Abstract

**Background:**

For patients with liver-confined metastatic colorectal cancer (mCRC), local therapy of isolated metastases has been associated with long-term progression-free and overall survival (OS). However, for patients with more advanced mCRC, including those with extrahepatic disease, the efficacy of local therapy is less clear although increasingly being used in clinical practice. Prospective studies to clarify the role of metastatic-directed therapies in patients with mCRC are needed.

**Methods:**

The Evaluating Radiation, Ablation, and Surgery (ERASur) A022101/NRG-GI009 trial is a randomized, National Cancer Institute-sponsored phase III study evaluating if the addition of metastatic-directed therapy to standard of care systemic therapy improves OS in patients with newly diagnosed limited mCRC. Eligible patients require a pathologic diagnosis of CRC, have *BRAF* wild-type and microsatellite stable disease, and have 4 or fewer sites of metastatic disease identified on baseline imaging. Liver-only metastatic disease is not permitted. All metastatic lesions must be amenable to total ablative therapy (TAT), which includes surgical resection, microwave ablation, and/or stereotactic ablative body radiotherapy (SABR) with SABR required for at least one lesion. Patients without overt disease progression after 16–26 weeks of first-line systemic therapy will be randomized 1:1 to continuation of systemic therapy with or without TAT. The trial activated through the Cancer Trials Support Unit on January 10, 2023. The primary endpoint is OS. Secondary endpoints include event-free survival, adverse events profile, and time to local recurrence with exploratory biomarker analyses. This study requires a total of 346 evaluable patients to provide 80% power with a one-sided alpha of 0.05 to detect an improvement in OS from a median of 26 months in the control arm to 37 months in the experimental arm with a hazard ratio of 0.7. The trial uses a group sequential design with two interim analyses for futility.

**Discussion:**

The ERASur trial employs a pragmatic interventional design to test the efficacy and safety of adding multimodality TAT to standard of care systemic therapy in patients with limited mCRC.

**Trial registration:**

ClinicalTrials.gov: NCT05673148, registered December 21, 2022.

**Supplementary Information:**

The online version contains supplementary material available at 10.1186/s12885-024-11899-2.

## Background

For patients with metastatic colorectal cancer (mCRC), surgical resection, when possible, has been associated with long-term progression-free survival (PFS) and overall survival (OS). Several large retrospective series have demonstrated 5-year OS rates of 40–70% in patients with isolated liver metastasis following liver metastasectomy [1–5]. Indeed, improvements in OS in patients with newly diagnosed mCRC over the last several decades have been attributed, in part, to an increase in hepatic resection [6]. For patients with limited extrahepatic disease, complete surgical resection has also been associated with prolonged PFS and OS, although the data are more limited [7–9]. While prospective evidence is lacking, these retrospective studies have demonstrated excellent long-term survival for patients with resectable mCRC and have defined the current standard of care (SOC).

In patients with multiorgan oligo-mCRC (e.g., low burden but liver inoperable disease or minimal extra-hepatic and/ or extra-thoracic disease), it is less clear whether local ablative therapies, including thermal ablation and stereotactic ablative radiation therapy (SABR), can provide clinical benefit such as durable control of disease or improve survival. Limited prospective data exist on the benefit of thermal ablation to all areas of inoperable hepatic disease. The CLOCC phase II randomized trial (EORTC-40,004) demonstrated that the addition of radiofrequency ablation to systemic therapy improved OS in patients with mCRC with inoperable liver disease (hazard ratio [HR] 0.58, 95% confidence interval [CI] 0.38–0.88, *p* = 0.01) [10, 11]. Multiple mature retrospective series have also reported high rates of local control and favorable long-term survival following the use of thermal ablation for CRC liver metastases [12–15].

SABR appears to be a safe and effective way to treat multiple metastatic sites in the lung, abdomen/pelvis, bone, and spine [16]. The use of SABR for the treatment of CRC lung and liver metastases has demonstrated local control rates of 80–90% with minimal toxicity [17, 18]. Additionally, there is emerging evidence that SABR to all sites of radiographic disease may improve PFS and OS [17, 18]. SABR-COMET was a randomized, phase II trial that demonstrated improved OS with SABR compared to the standard of care arm (median OS 41 vs. 28 months, HR 0.57, 95% CI 0.30–1.10, *p* = 0.090), although having 4.5% grade 5 treatment-related adverse events in the SABR arm. While SABR-COMET was designed as a tumor-agnostic trial in 99 patients with up to 5 metastatic lesions, 27% (*n* = 9) of the patients in the control group and 14% (*n* = 9) in the SABR group had a CRC primary [19, 20]. In addition to SABR-COMET, multiple other trials have shown the benefit of SABR in the oligometastatic setting including non-small cell lung cancer, prostate, and renal cell carcinoma [21–25]. These studies demonstrate that SABR is a safe and highly effective locoregional therapy that improves oncologic outcomes in a variety of disease settings, including in some settings where an oligometastatic paradigm has not been well established, in contrast to CRC. In fact, to date there are no completed randomized clinical trials investigating the benefit of SABR in patients with mCRC.

High quality data on the utilization of multimodality metastatic-directed therapy, including the combination of surgical resection, thermal ablation, and SABR, for patients with mCRC is limited despite increased use in clinical practice. A recent prospective Finnish interventional study (RAXO study) highlights the potential for multimodality directed therapy in patients with metastatic CRC [26]. The 5-year OS for patients treated with systemic therapy alone was 6% compared to 40% for patients treated with local ablative therapies and/ or surgical debulking (i.e., R2 resection) [26]. A 5-year survival of 40% with multimodality metastatic-directed therapy is quite notable, as for context the 5-year survival for patients who underwent metastasectomy (R0/R1 resection) was in comparison 66%. These data suggest that local metastatic-directed therapy with SABR, thermal ablation, and surgery may significantly enhance cancer control and enhance overall survival in patients with mCRC rather than continuing with systemic therapy alone.

ERASur was jointly developed by the National Cancer Institute (NCI)’s Alliance for Clinical Trials in Oncology and NRG Oncology to evaluate multimodality metastases-directed therapy in patients with mCRC. Despite the long history of treating oligometastatic CRC, questions remain regarding the benefit of extending local metastatic-directed therapies to patients with more extensive metastatic disease including in patients with extrahepatic disease. The ERASur trial seeks to fill this gap by testing if total ablative therapy (TAT) to all sites of metastatic disease improves survival using a pragmatic design that integrates the current spectrum of multimodality local therapies. If the addition of TAT to SOC systemic therapy improves OS, it will be established as a new standard of care for patients with limited mCRC. If TAT is associated with increased toxicity without improving OS, then future treatment paradigms can avoid unnecessary toxicity associated with TAT.

## Methods/design

### Study objectives

The primary objective of ERASur is to compare the outcome of using TAT in addition to SOC systemic therapy versus SOC systemic therapy alone in terms of OS, measured from the time of randomization, in patients with newly diagnosed limited mCRC. The secondary objectives include evaluating event-free survival, adverse events, and time to local recurrence for patients treated with TAT, defined as the time from the end of TAT to the date of first documented recurrence at any disease site treated with TAT.

### Study setting

ERASur is co-led by the Alliance for Clinical Trials in Oncology and NRG Oncology through the NCI National Clinical Trials Network (NCTN) and supported by the Southwest Oncology Group (SWOG) and the Eastern Cooperative Oncology Group-American College of Radiology Imaging Network (ECOG-ACRIN) Cancer Research Group. Patients will be accrued from member institutions of these NCTN cooperative groups which includes community and academic sites. NCI Central Institutional Review Board (CIRB) approved the study, with participating institutions relying on the CIRB. All patients must provide written informed consent.

### Study design

ERASur is a two-arm, multi-institutional, randomized phase III study investigating the effect of the addition of TAT to SOC systemic therapy in patients with limited mCRC. The study schema is illustrated in Fig. 1.

**Fig. 1 Fig1:**
[figure not shown]
ERASur trial schema

### Patient selection and eligibility criteria

Patients 18 years of age or older with histologically confirmed mCRC with 4 or fewer sites of metastatic disease are eligible. Metastatic sites must be radiographically evident, but pathologic confirmation is not required. Single sites include: each hemi-liver (right and left), each lobe of the lungs, each adrenal gland, lymph nodes amenable to a single resection or treatment in a single SABR field, and bone metastases amenable to treatment in a single SABR field. Patients with liver-only metastatic disease are not eligible, nor are patients whose tumors are known to have *BRAF V600E* mutations or microsatellite unstable. Metastatic lesions must be amenable to any combination of surgical resection, microwave ablation (MWA), and/or SABR. SABR is required to at least one site. Detailed eligibility criteria are shown in Table 1. Patients will have the option of pre-registering for the study within 16 weeks of starting first-line SOC systemic therapy with regimens including 5-fluorouracil, leucovorin, and oxaliplatin (mFOLFOX6), capecitabine and oxaliplatin (CAPOX), 5-fluorouracil, leucovorin, and irinotecan (FOLFIRI), and 5-fluorouracil, leucovorin, oxaliplatin, and irinotecan (mFOLFOXIRI) with or without anti-VEGF or EGFR therapies. For registration, a minimum of 16 weeks and a maximum of 26 weeks of first-line systemic therapy is required. Patients with overt disease progression after 16–26 weeks of first-line systemic therapy are not eligible for the study and if pre-registered will be removed. The study calendar is shown in Table 2.

**Table 1 Tab1:** Eligibility Criteria

1. Age ≥ 18 years.
2. Eastern Cooperative Oncology Group Performance status of 0–2.
3. Histologically confirmed metastatic colorectal adenocarcinoma.
4. No known microsatellite instable (MSI) tumor.
5. No known BRAF V600E mutation.
6. No known peritoneal and/or omental metastases.
7. Primary tumor is already resected or amenable to resection.
8. 4 or fewer apparent sites of metastatic disease based on review by local medical team of baseline radiographic imaging obtained prior to initiation of systemic therapy. Single sites include: a. Each hemi-liver (right and left). b. Each lobe of the lungs. c. Each adrenal gland. d. Lymph nodes amenable to a single resection or treatment in a single stereotactic ablative radiation therapy (SABR) field. e. Bone metastases amenable to treatment in a single SABR field.
9. Liver-only metastatic disease is not permitted.
10. Metastatic lesions must be amenable to any combination of surgical resection, microwave ablation, and/or SABR. SABR is required for at least one lesion.
11. Measurable disease per RECIST v1.1.
12. No overt evidence of disease progression during systemic therapy prior to registration.
13. Not eligible for hepatic artery infusion pump (HAIP) therapy or benefit of HAIP therapy is undefined.
14. Received first-line systemic therapy for metastatic disease for a minimum of 16 weeks and a maximum of 26 weeks.
15. Prior definitive therapy, including adjuvant chemotherapy, must have been completed at least 12 months prior to diagnosis of metastatic disease.
16. No pregnant or nursing patients.
17. No other planned concurrent investigational agents while on study.
18. Required initial laboratory values: a. Absolute neutrophil count ≥ 1,500/mm^3^ b. Platelet count ≥ 50,000/mm^3^ c. Creatinine ≤ 1.5 x upper limit of normal (ULN) or calculated creatinine clearance ≥ 30 mL/min d. Total bilirubin ≤ 1.5 x ULN e. AST(SGOT)/ALT(SGPT) ≤ 3.0 x ULN– if metastatic liver disease, ≤ 5 x ULN

**Table 2 Tab2:** Study calendar. pre-study testing to be completed ≤ 28 DAYS before registration: scan of any type which is used for tumor measurement per protocol, all laboratory studies and history and physical

	Prior to Pre-Registration	Day 1 of each cycle of systemic therapy*	Prior to Registration/Randomization*	During Total Ablative Therapy (TAT) **	During Standard of Care Treatment (SOC) **	Follow-up***
Tests & Observations						
History & Physical, weight, performance status		X	X	X	X	X
Height			X			
Pulse, Blood Pressure		X	X	X	X	
CTCAE Adverse Event Assessment		X(1)	X(1)	X(1)	X(1)	X(1)
Laboratory Studies						
CBC including Differential		X	X	X	X	X
Comprehensive Metabolic Panel		X(2)	X(2)	X(2)	X(2)	X(2)
Serum or Urine HCG			X(3)			
CEA			X(4)			X(4)
CD4 count			X(5)			
Staging						
CT chest, CT (or MRI) abdomen/pelvis (or PET/CT)	A	B	B	B	B	B

* Labs completed prior to registration may be used for Day 1 of Cycle 1 of the next planned cycle of systemic therapy (if registration occurs prior to initiation of systemic therapy) if obtained ≤ 14 days prior to treatment. For subsequent cycles, labs, scans, tests, and observations may be obtained ≤ 3 business days prior to day of treatment

** For patients on Arm 1, physical examination, vitals, adverse event (AE) assessment, and labs are required at 14–18 weeks post-randomization. For patients on Arm 2, physical examination, vitals, AE assessment and labs are required at least prior to the start of each cycle for patients receiving active systemic therapy and 14–18 weeks post-randomization. For patients on a treatment break, physical examination, vitals, AE assessment and labs are required at 14–18 weeks post-randomization

*** Following the first assessment timepoint at 14–18 weeks post-randomization, patients should undergo physical examination, AE assessment, labs, and staging scans every 3 months (+/- 1 month) until disease progression or start of off-protocol anticancer therapy, whichever comes first. Off-protocol anticancer therapy incudes any experimental agent, a systemic therapy regimen not specifically included outlined in the protocol, or, for patients randomized to Arm 2 (institutional SOC therapy), local metastatic-directed therapy other than what is delivered for palliation. Patients who discontinue study treatment due to disease progression (or who start a new anticancer therapy after discontinuing study treatment for reasons other than disease progression) should be followed every 6 months for survival until 5 years after registration

1 Solicited adverse events are to be collected starting prior to treatment until off-treatment. Routine adverse events are to be collected starting after registration until the end of survival follow-up. For patients who register before/during systemic therapy, the first routine adverse event assessment should take place after registration but prior to Day 1 of the next planned cycle of systemic therapy

2 Albumin, alkaline phosphatase, total bilirubin, bicarbonate (or total CO2), BUN, chloride, creatinine, glucose, potassium, total protein, SGOT (AST), SGPT (ALT), and sodium

3 For women of childbearing potential. Must be done ≤ 14 days prior to registration

4 Perform at baseline (prior to initiation of systemic therapy, if applicable), ≤ 28 days prior to registration, ≤ 28 days prior to randomization, 14–18 weeks post-randomization, then every 3 months (+/- 1 month) for the first three years after randomization, then every 6 months (+/- 1 month) for years 4–5 after registration. Any measurements of biochemical response should occur in conjunction with the radiologic assessments for disease status

5 To be performed ≤ 28 days prior to registration only for patients with known HIV positivity

A Baseline scans should include CT chest and CT or MRI of the abdomen/pelvis. The CT component of a PET-CT is also acceptable if the CT is of diagnostic quality (using oral and IV contrast if possible). CT scans should be of diagnostic quality and performed with oral and IV contrast unless there is a medical contraindication. MRIs should be performed with IV contrast unless there is a medical contraindication. For patients who register after initiation of induction systemic therapy, baseline imaging obtained ≤ 28 days prior to initiation of systemic therapy must be available. For patients with liver disease, triple-phase CT or MRI with IV contrast can be obtained for treatment planning as directed by the treating physician

B Response assessment should include assessment of all sites of disease and the same imaging method used at baseline must be used for all subsequent scans. The first response assessment imaging time point is 14–18 weeks post-randomization. Imaging should then be obtained every 3 months (+/- 1 month) until evidence of progression or relapse

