MWA can be delivered either intra-operatively or using a percutaneous approach. Multiple electrodes and overlapping ablations will be permitted to ensure adequate coverage of the target. A minimum margin of 5.0 mm will be required for lesions treated with MWA on this study. Initial assessment of the ablation zone will be verified immediately intra-procedurally using ultrasound, computed tomography (CT), or magnetic resonance imaging (MRI). If a margin of < 5.0 mm is observed at initial assessment, additional ablation will be attempted to extend the ablation zone, expand the area of insufficient coverage and provide for at least 5.0 mm minimal margin around the target tumor. If at the first imaging timepoint the tumor is deemed to be incompletely covered, the tumor can undergo repeat treatment without penalization. As quality assurance, the study team will review pre-treatment imaging, the procedure notes, and adverse events within 30 days of treatment associated with MWA. Imaging from the first assessment timepoint at 14–18 weeks post-randomization will also be reviewed to ensure completion of planned ablation.

Lesions that are too small to be treated with any of the modalities included in TAT will be monitored and treated if they progress to a size that is amenable to treatment, and they will not be considered as Response Evaluation Criteria in Solid Tumors (RECIST) progression. Following completion of TAT, the treating healthcare team will consider re-starting systemic therapy within 2 weeks if no surgery is performed or within 4 weeks if surgery is included as part of TAT. Use of maintenance systemic therapy or systemic therapy breaks is permitted at the discretion of the treatment team. Patients randomized to arm 1 with the primary tumor intact will have the primary tumor removed within 6 months of randomization. Resection of the primary tumor may be performed at the same time as metastasectomy or may be staged per discretion of the healthcare team. For patients with primary rectal cancers, the use of pre-operative radiation or chemoradiation will be left to the discretion of the healthcare team.

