### Assessment and follow-up

Radiologic response will be evaluated using the RECIST version 1.1 guidelines [27]. A local recurrence will be defined differently based on the modality of treatment. For patients treated with SABR, a recurrence will be deemed local if located in or directly adjacent to the planning target volume. For a site treated using MWA, a recurrence will be deemed local if it is within 1 cm of the treatment site. For patients who undergo surgery, a recurrence will be considered local if it is located at the margin of resection.

Adverse events (AEs) will be graded using the Common Terminology Criteria for Adverse Events (CTCAE) Version 5.0. Solicited AEs will be collected at baseline prior to treatment until off treatment. Routine AEs will be collected starting after registration until the end of survival follow-up. The first treatment response assessment timepoint will be at 14–18 weeks post-randomization, and then every 3 months until disease progression or at the start of off-protocol anticancer therapy. Off-protocol anticancer therapies consists of any investigational agent, systemic therapy regimen(s) not included in the protocol; for patients randomized to arm 2, this includes any local metastatic-directed therapy other than therapy delivered with palliative intent. All visits will include a history and physical examination, laboratory studies, AE assessment, and imaging with CT of the chest along with CT or MRI of the abdomen and pelvis or, alternatively, a positron emission tomography/computed tomography (PET/CT). All patients, irrespective of whether continuing on study, or who are receiving off protocol therapy, will be followed for OS (except patients who withdraw consent).

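### Table 2 and the text give conflicting rules for when staging scans stop, and one stopping trigger applies in arm 2 only, putting event-free survival at risk of unequal ascertainment

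*Protocol article*

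**What the plan says.** Three places in the protocol article govern when scheduled staging scans end.

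- **Table 2, triple-asterisk footnote (Follow-up column):** "staging scans every 3 months (+/- 1 month) until disease progression or start of off-protocol anticancer therapy, whichever comes first".
- **Assessment and follow-up:** after the first assessment, "then every 3 months until disease progression or at the start of off-protocol anticancer therapy".
- **Table 2, footnote B (imaging row):** "Imaging should then be obtained every 3 months (+/- 1 month) until evidence of progression or relapse".

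The first two also define off-protocol therapy. Experimental agents and systemic regimens outside the protocol count in both arms. One further item is specific to an arm: "for patients randomized to Arm 2 (institutional SOC therapy), local metastatic-directed therapy other than what is delivered for palliation" in the footnote, and "for patients randomized to arm 2, this includes any local metastatic-directed therapy other than therapy delivered with palliative intent" in the text.

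Patients who stop study treatment because of progression, or who start a new anticancer therapy after stopping it for another reason, "should be followed every 6 months for survival until 5 years after registration".

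In arm 1, the Treatment plan says that lesions initially too small for ablation "will be monitored and treated if they progress to a size that is amenable to treatment", and that this is not RECIST progression.

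EFS is named as a secondary endpoint in the Abstract and under Study objectives. The article does not list its events or give a censoring rule. Overall survival is followed in all patients whatever therapy they receive, unless consent is withdrawn.

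**The concern.** A patient who starts off-protocol therapy without progression is no longer scanned on schedule under two of these passages, but still is under the third. Both Table 2 footnotes apply to the same follow-up imaging cell, so two sites could handle the same patient differently and each point to the table.

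The stop also depends partly on arm. Further local treatment of a metastasis can leave an arm 1 patient on the scan calendar. In arm 2 it ends scheduled scanning, unless it is palliative. Every randomised patient must have lesions amenable to ablation, the assignment is evident to patient and clinician, and the Abstract says that local therapy is increasingly used in practice. Off-protocol local therapy in arm 2 is therefore plausible.

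At stake is the progression component of EFS, the first-listed secondary endpoint. An analysis plan can choose to censor at the switch or count it as an event. It cannot recover scans that were never scheduled or collected.

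**Working it through.** **1. The passages side by side**

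| Situation before progression | Triple-asterisk footnote; Assessment and follow-up | Footnote B |
|---|---|---|
| Experimental agent or non-protocol systemic regimen, either arm | scans stop | scans continue |
| Non-palliative local therapy, arm 2 | scans stop | scans continue |
| Later treatment of an initially too-small lesion, arm 1 | scans continue | scans continue |
| No off-protocol therapy | scans continue | scans continue |

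The rules disagree in the first two rows. The arms differ between the second and third.

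**2. The plan's own figures**

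The article gives no event count, power or hazard ratio for EFS, so there is nothing to reproduce for that endpoint. The overall survival design does reproduce. Without interim looks, power = Φ(|ln 0.7| × √(208/4) − 1.645) = Φ(2.572 − 1.645) = Φ(0.927) = 0.823. With futility looks at 25% and 50% of events under Rho = 1.5 beta spending, it is 0.8006 against the stated 80%. The scan rule does not touch these figures, because deaths are followed regardless.

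**3. Illustration for EFS**

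The following assumptions are not in the documents:

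- EFS is exponential with a control median of 9 months.
- A share p₂ of arm 2 and p₁ of arm 1 start off-protocol therapy 0–6 months before the progression that it anticipates.
- The true hazard ratio (TAT versus control) is 1.00 or 0.70.

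There is a simple ceiling if patients are censored immediately before progression. The observed hazard in each arm is then (1 − p) times the true one, so the hazard ratio is multiplied by (1 − p₁)/(1 − p₂). Estimates for the 0–6 month lead come from fitting a Cox model to large simulated samples.

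| p₂ / p₁ | Ceiling multiplier | Censored, true 1.00 | Censored, true 0.70 | Counted as event, true 1.00 | Counted as event, true 0.70 |
|---|---|---|---|---|---|
| 10% / 0% | 1/0.90 = 1.11 | 1.09 | 0.76 | 0.98 | 0.69 |
| 20% / 0% | 1/0.80 = 1.25 | 1.20 | 0.84 | 0.96 | 0.68 |
| 20% / 10% | 0.90/0.80 = 1.125 | 1.10 | 0.77 | 0.98 | 0.69 |
| 10% / 10% | 0.90/0.90 = 1.00 | 1.00 | 0.70 | 1.00 | 0.70 |

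The simulated effect lies below the ceiling because censoring removes person-time as well as events. If the switch instead falls uniformly over the time to progression, the censoring multiplier drops to roughly 1.05–1.06 at 10% / 0% and 1.12–1.13 at 20% / 0%. A longer gap also enlarges the opposite shift when the switch is counted as an event. If the switch is unrelated to prognosis, censoring gives a multiplier of 1.00.

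**The case against.** The strongest reply has four parts.

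- **The passages can be read together.** The triple-asterisk footnote governs the whole follow-up visit, and footnote B mainly fixes imaging method and interval. The former may simply add a stop that the latter leaves out. That reading is possible, and the text section supports it. But footnote B states its own end point for imaging, so the table still gives two answers.
- **The arm difference is largely inherent.** Local therapy is the assigned treatment in arm 1 and is barred in arm 2 except for palliation. A symmetric definition would label the experimental treatment itself off-protocol. This stands as a defence of the definition of off-protocol therapy. It does not explain why that definition should end the collection of scans.
- **The bias is not shown.** A reader might infer that EFS is informatively and unequally censored, to the disadvantage of TAT. The documents do not support that. They give no EFS censoring rule, no switching rates and no reasons for switching. Control patients who obtain ablation before progression could be those doing well, and censoring them would push the other way. Switches at or after progression cost nothing, because scheduled scans have already ended in both arms. This part stands in full.
- **The loss is partial and secondary.** Deaths are still captured, many such patients will be scanned in routine care, and the primary endpoint is untouched. This also stands, and it limits the weight of the point.

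**Conclusion.** The conflict between the passages and the arm-specific trigger are established by the text. Under the stopping rule in the triple-asterisk footnote and the Assessment and follow-up section, progression after off-protocol therapy is not collected on schedule. EFS is therefore at risk of unequal, possibly informative ascertainment. It is not shown to be biased.

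The multiplier of about 1.1–1.2 rests on the assumed 10–20% switching in arm 2, none in arm 1, and censoring shortly before progression. A reader might take the ceiling of 1.11–1.25 as the expected effect. It applies only when censoring is almost simultaneous with progression and arm 1 loses nothing.

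The primary analysis, the sample size and the interim looks do not change. The point is still worth acting on, because the trial is enrolling and uncollected scans cannot be restored by a later analysis decision.

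**What to change.** Reconcile the triple-asterisk footnote, footnote B and the Assessment and follow-up section into a single imaging-collection rule for both arms. Scan results should continue to be collected on the same calendar until RECIST progression or death, whatever off-protocol therapy is started. The definition of off-protocol therapy can stay as it is. It would simply no longer end data collection for the endpoint.

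EFS could then be analysed irrespective of the switch, as well as under whatever censoring or event rule the analysis plan sets. The date and type of the first off-protocol therapy should be recorded by arm, so that switching can be reported.

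The cost is a small amendment and some additional scan reports, mostly from routine care. Treatment is not affected.
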